#### Telephone call attention placebo

The telephone call attention placebo lasts 15 weeks, with one telephone call scheduled each week. PhD candidates, who are trained clinical psychologists, conduct the telephone calls. The telephone contact has no treatment intention, and will follow an interview guide with the questionnaire GAD-7 and talking points such as “How was your week?” and “Do you have any plans for the week-end?”. Each call lasts no longer than 20 min. The intention of the telephone call attention placebo is to control for the extra therapist contact in the physical exercise condition, and to ensure that participants spend approximately the same net amount of time in direct therapist contact across the treatments. The first 5 weeks of telephone call attention placebo is an initial phase of treatment. During the following 10 weeks, telephone calls are combined with CBT.

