**Methods:**

The sample comprises 70 participants aged 60–75 years, who have GAD. Exclusion criteria comprise substance abuse and unstable medication; inability to participate in physical exercise; and conditions which precludes GAD as primary diagnosis. The interventions are individual treatment in the outpatient clinic at the local psychiatric hospital, with two experimental arms: (1) CBT + physical exercise and (2) CBT + telephone calls. The primary outcome measure is symptom reduction on the Penn State Worry Questionnaire. Other measures include questionnaires, clinical interviews, physiological, biological and neuropsychological tests. A subset of 40 participants will undergo magnetic resonance imaging (MRI). After inclusion, participants undergo baseline testing, and are subsequently randomized to a treatment condition. Participants attend five sessions of the add-on treatment in the pre-treatment phase, and move on to interim testing. After interim testing, participants attend 10 sessions of CBT in parallel with continued add-on treatment. Participants are tested post-intervention within 2 weeks of completing treatment, with follow-up testing 6 and 12 months later.

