## Method

### Study design

The study is a 2 × 2 mixed factorial design (Time x Group) with participants randomized to one of two treatment conditions: (1) CBT combined with physical exercise (CBT + PE) or (2) CBT combined with telephone call attention placebo (CBT + AP). Participants complete pre-treatment, interim and post-treatment outcome measures, in addition to follow-up tests at 6 and 12 months after treatment.

Participants in both treatment conditions attend a 5-week pre-treatment period. The pre-treatment period has a two-part rationale. The first 5 weeks of physical exercise are aimed at introducing the participant to the exercises with a focus on adjustment and neuromuscular facilitation [64]. In addition, resting BDNF has been shown to increase after 5 weeks of physical exercise [65]. The primary goal of the pre-treatment period is to ensure good implementation of physical exercise, and to obtain elevated resting BDNF in the CBT + PE group before the onset of CBT. As such, the pre-treatment period is a measure to facilitate the add-on effects of physical exercise.

Participants receiving CBT + PE attend one supervised and two unsupervised sessions of PE during each of the 5 weeks of the pre-treatment period. Participants receiving CBT + AP receive one telephone call per week during the pre-treatment period.

After the pre-treatment period, the participants receive 10 weekly sessions of CBT combined with either continued physical exercise in the participants receiving CBT + PE or weekly telephone contact in parallel to the CBT sessions in the participants receiving CBT + AP. See Fig. 1 for a display of the study design. The present protocol has been prepared in accordance with relevant items from the Standard Protocol Items: Recommentations for Interventional Trials (SPIRIT) Checklist (see Additional file 1). See Fig. 2 for the SPIRIT figure displaying the schedule of enrolment, interventions and assessments.

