#### Physical exercise (PE)

The duration of the PE programme is 15 weeks. The first 5 weeks comprise the pre-treatment intervention. During the following 10 weeks the participants attend to both PE and CBT. Each week consist of one supervised training session at the local mental health facility (clinic), and two individual training sessions. Supervised sessions are led by physiotherapists or occupational therapist who are trained in the study manual and receive supervision on test procedures and the exercise manual. For the individual training sessions, each participant is given their own exercise journal with instructions, and is instructed to log each individual training session. All participants use a heart rate monitor watch [96], which is used during individual endurance training sessions and monitored by the PE therapist at the supervised training session. This is a measure of patient adherence to the PE. Physical tests at the interim and post testing time points also serve as manipulation checks. The participants complete the GAD-7 questionnaire at each of the supervised training sessions.

The PE programme is adjustable according to the participants’ prerequisites, without compromising the exercise intensity. Each session lasts approximately 45–60 min, and contains both strength and endurance training. The strength training programme consists of seven exercises; squats, push-ups, lunges, rowing with elastic bands, calf raises, dips and shrugs with elastic bands. Endurance training is designed based on interval principles. The exercise intensity progresses every fifth week. The intensity level at the beginning of the intervention period (week 1–5) will be low to moderate (65–85% of maximum heart rate (HR max)). It increases to moderate intensity at week 6–10 (65–90% of HRmax) and at week 11–15 it increases to moderate to high intensity (65–95% of HRmax). This equals 60–70%, 70–80% and 80–90% of one repetition maximum (1RM) [97] when transferred to resistance load in strength exercises [98]. The exercise programme is designed to ensure that participants take part in at least the minimal therapeutic dose of exercise, which is 150 min of moderate intensity activity per week [99, 100].

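### The calls match the exercise arm on the number of weekly therapist contacts, but the schedules do not show the similar contact time that the protocol says they are meant to ensure

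*Protocol article*

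**What the plan says.** All references are to the protocol article.

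- **Purpose of the calls** (Telephone call attention placebo). They are to control for the extra therapist contact that comes with exercise, and "to ensure that participants spend approximately the same net amount of time in direct therapist contact across the treatments".
- **Dose of the calls** (same section). One a week for 15 weeks, with a ceiling: "Each call lasts no longer than 20 min". On the provider: "PhD candidates, who are trained clinical psychologists, conduct the telephone calls".
- **Dose of the exercise** (Physical exercise (PE)). For 15 weeks, each week has "one supervised training session at the local mental health facility (clinic), and two individual training sessions". On length: "Each session lasts approximately 45–60 min". On the provider: "Supervised sessions are led by physiotherapists or occupational therapist".
- **Format** (Abstract, Methods). "The interventions are individual treatment in the outpatient clinic at the local psychiatric hospital".
- **First five weeks** (Study design). Before CBT begins, exercise participants "attend one supervised and two unsupervised sessions of PE during each of the 5 weeks of the pre-treatment period"; the other arm gets one call a week.
- **CBT** (Cognitive behaviour therapy (CBT)). Ten individual sessions and one introductory session, the same in both arms. Session length is not given.
- **Discussion.** The authors say they try to control for human contact through the calls, and they accept that extra attention might make CBT work better.

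**The concern.** The statement of purpose is about time, but the schedules line up only on frequency and span: 15 weekly contacts in each arm. Minutes per contact differ, and no sentence links the two schedules to the stated aim.

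This bears on interpretation. The Background calls the comparator a placebo control condition, and the Discussion attributes the expected benefit to exercise acting through cognition, brain-derived neurotrophic factor and heart rate variability. The same Discussion names added attention as something that could itself improve outcome. The primary outcome, the PSWQ, is self-reported. A reader who takes contact time as equalised would rule out attention as a partial explanation of a benefit, and the schedules do not support ruling it out. The limitations listed in the Discussion do not mention contact time.

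**Working it through.** The article states no total contact time, so there is no figure of its own to reproduce. The check is arithmetic on the schedules. The two unsupervised exercise sessions a week are left out because no therapist is present.

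**1. Scheduled add-on minutes** = contacts per week × weeks × minutes per contact.

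- Exercise: 1 × 15 × 45 = 675 min; 1 × 15 × 60 = 900 min.
- Calls: 1 × 15 × 20 = 300 min at most.
- Difference: 675 − 300 = 375 min; 900 − 300 = 600 min. CBT is common to both arms and does not change this difference.
- Ratio: 675/300 = 2.25; 900/300 = 3.0. This holds only if the whole supervised session counts as contact.

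**2. Break-even share.** The share of a session that must be direct contact for the add-ons to be equal is call length / session length.

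- Calls at the full 20 min: 20/60 = 33%; 20/45 = 44%.
- Calls averaging 15 min (assumed): 15/60 = 25%; 15/45 = 33%. Because 20 min is a ceiling, shorter calls lower the share needed.

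**3. If half of each session counts (assumed).** 337.5/300 = 1.13; 450/300 = 1.5.

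**4. Total contact including CBT.** This uses 11 CBT contacts (10 sessions plus the introductory one). Their length is not given, so 45, 60 and 90 min are assumed, adding 495, 660 or 990 min to each arm. Each cell gives the exercise/call ratio for 45-min to 60-min exercise sessions, with calls at 20 min.

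| CBT length (assumed) | Half of session counts | Whole session counts |
|---|---|---|
| 45 min | 832.5/795 = 1.05 to 945/795 = 1.19 | 1170/795 = 1.47 to 1395/795 = 1.75 |
| 60 min | 997.5/960 = 1.04 to 1110/960 = 1.16 | 1335/960 = 1.39 to 1560/960 = 1.63 |
| 90 min | 1327.5/1290 = 1.03 to 1440/1290 = 1.12 | 1665/1290 = 1.29 to 1890/1290 = 1.47 |

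If calls average 15 min (225 min in all), the ranges become 1327.5/1215 = 1.09 to 945/720 = 1.31 for half, and 1665/1215 = 1.37 to 1395/720 = 1.94 for whole.

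**5. The five weeks before CBT.** The add-on is the only scheduled treatment contact here.

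- Exercise: 5 × 45 = 225 min; 5 × 60 = 300 min. If half counts: 112.5–150 min.
- Calls: 5 × 20 = 100 min at most.

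The exercise arm has the larger figure in every case computed in steps 1 and 3 to 5. The size depends mainly on the contact share, which the article does not give.

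**The case against.** The sentence states an intention and is heavily qualified: roughly equal, net, direct contact. Net may well mean that time spent on strength or interval work is not counted. If half of a session counts and CBT is included, the totals differ by only 3–19% with full-length calls, which could fairly be called similar. The meaning of net, the length of a CBT session and the interaction within an exercise session may be set out in the full protocol or the manuals, which are not shown, so their absence is no fault in a condensed article. The direction of any attention effect is also open: a one-to-one talk with a clinical psychologist may do as much for worry as physical coaching. Both kinds of add-on provider refer CBT questions back to the CBT therapist, and compliance is registered and will be analysed separately.

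Much of this stands. A reader might infer that the protocol contradicts itself, or that exercise participants certainly receive two to three times the contact. The documents support neither. The ratio of 2.25–3 needs every minute of a supervised session to count and CBT to be left out, and the article does not say how much of a session is interaction.

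The objection does not supply support for the aim as stated. Add-on equality needs a share of 33–44% or less with every call at its ceiling. The article describes the sessions as led by therapists, in individual treatment, and gives no reason to suppose so low a share. CBT cannot narrow the ratio in the first five weeks. Registered compliance would show attendance, not minutes.

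**Conclusion.** The concern holds in limited form. The article matches the arms on the number and span of add-on contacts. It does not show that contact time is similar, and the schedules suggest that exercise participants probably receive more. Scheduled add-on time is 675–900 min against at most 300 min, and 225–300 min against at most 100 min before CBT. Net contact could be close or well apart. Across the assumptions tried, the ratio of total contact runs from about 1.03 (half the session counts, 90-min CBT, full-length calls) to 1.94 (whole session, 45-min CBT, 15-min calls).

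A reader might go further and conclude that the trial's comparison is biased. That does not follow. Randomisation still gives a valid comparison of CBT plus exercise with CBT plus calls. What is limited is the step from a PSWQ difference between the packages to an effect of exercise itself, since added in-person contact remains a possible partial explanation of unknown size. The change is worth making, but it does not touch the sample size, the schedule or the primary analysis. Confidence is moderate, because the share of each session that is direct contact is not known.

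**What to change.** 1. Reword the purpose of the calls: weekly contact frequency is matched, and the calls control for added contact only in part, because scheduled session length and mode (in person against telephone) differ. The wording should not assert that net contact time is unequal, since that has not been measured.
2. Log the direct therapist contact minutes of each add-on session and each call, next to the compliance already registered, and report them by arm with the primary result.
3. Unless those minutes prove similar, word the main conclusion as the effect of adding supervised exercise, with its accompanying therapist contact, to CBT.

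The cost is one more logged variable and a somewhat narrower causal claim. If logging comes too late for some participants, the first step still applies and the narrower conclusion should be used.

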### Recruitment and eligibility

We will recruit participants through primary health care services and the media. Assessment for the trial requires a formal referral from a primary physician to the hospital. The project coordinators apply the following interviews with potentially eligible participants: the M.I.N.I. [66, 67], the GAD-module from ADIS-IV [63] and the MMS-E [68]. If eligible for inclusion, participants sign an informed consent form, and complete self-report baseline measures. Furthermore, the project coordinators obtain written approval for participation from the participants’ primary physician to ensure their safety in participating in physical testing and exercise. The project coordinators schedule baseline testing once the primary physician has medically cleared the participant.

### Data management and security

Each potential participant is assigned a unique identification number at the start of the assessment. Only the project coordinators have access to the connecting key, which we store at a separate domain on a secure research server. We handle all data according to internal procedures, and store data on the hospital regional secure research server. We store biological material in a research-specific biobank in accordance with the Regional Committee for Medical and Health Research Ethics procedures. We will anonymize all data 5 years after trial completion.

### Ethical considerations

The participants meet several persons during assessment, testing and treatment. Thus, to create predictability, continuity and safety, each participant is allocated a project coordinator who is responsible for their clinical pathway. Challenges and adverse events during treatment are handled by the project coordinator according to internal procedures. The project coordinator also has a closing conversation with the patient at the end of treatment to inform participants about follow-up testing and give them the opportunity to give feedback on treatment and research participation. The assessments at each test point in the study are allocated across several days to minimise strain on participants.

The development of cognitive impairment can become evident during the assessment phase. This can cause participants stress and potentially aggravate psychiatric symptoms. In cases where we document cognitive impairment during the initial assessment, the project coordinator excludes the participant from further participation. The project coordinator offers to refer the participant to gerontopsychiatric services.

If conditions that exclude patients from participating in the study are disclosed or develop during treatment, the participant will be discontinued from trial participation. In such cases, the participant will continue treatment or be referred for other suitable treatment, depending on the reason for discontinuing trial participation. If patients are in acute need of further treatment following ordinary trial termination, they are offered services as necessary at Solli DPS or other suitable facilities. All participants are insured through The Norwegian Patient Injury Compensation.

We conducted a feasibility study of four participants who received CBT + PE in March 2016 to August 2017. One of the ethical arguments for conducting the feasibility study was to ensure that the total load of testing and treatment was within the limits that the participants could tolerate. We also wanted to test the coordination of testing and treatment. Results from the feasibility study have been presented at two conferences. Further, we presented preliminary results and our experiences with the implementation of the physical exercise protocol at the 7th International Conference of Physiotherapy in Psychiatry and Mental Health in Reykjavik [101]. We presented the feasibility study and results at the 48th Annual Congress of the European Association for Behavioural and Cognitive Therapies [102]. Our conclusions from the feasibility study are that the combination of physical exercise and CBT appears to be feasible and potentially beneficial in our target population.

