### Participants

Adults, aged 60–75 years (*n* = 70), who have a primary diagnosis of GAD as evaluated by the ADIS-IV [63] will be included. Exclusion criteria are (1) substance abuse; (2) use of benzodiazepines and antipsychotic medication; (3) changes in the dose of other psychotropic medication during the study; (4) medical conditions that preclude participation in physical exercise; (5) severe major depression as determined by the Mini International Neuropsychiatric Interview (M.I.N.I.) [66, 67]; (6) life-time history of psychosis and/or mania; (7) participation in other ongoing psychotherapy; (8) organic brain disease; (9) a score of 25 or less on the Mini Mental State Examination (MMS-E) [68] and (10) participation in physical exercise exceeding 75% of the exercise dose given in the study.

A subsample of 40 participants, who do not the meet exclusion criteria for magnetic resonance imaging (MRI), will be included in a nested MRI study. The exclusion criteria for MRI are (1) MRI-incompatible metal screws or implants; (2) large tattoos on head, neck or upper body; (3) pacemaker and (4) claustrophobic fear, to a degree whereby participants refuse to undergo MRI without sedatives. These exclusion criteria are applied to ensure patient safety.

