#### Randomisation

Randomisation is performed anonymously at the University of Bergen in blocks of ten following baseline testing. Randomisation is computerised and concealed [94]. The person conducting the randomisation is blind to participants’ identities and does not have any information on the participants. Blocks of ten were preferred, to achieve predictability for the hospital and staff. This does, however, mean that for every block, the tenth allocation can be determined with certainty if that of the former nine is tracked. Calculations using hypergeometric distributions also show that there is a 4.76%, 16.66% and 44.44% probability that the precise allocation of participants can be known with certainty following 6, 7 and 8 draws respectively. However, information about allocation is not tracked, and was deemed an acceptable risk to achieve practical feasibility of running the trial within a clinical setting.

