#### Post-treatment testing

Post-treatment testing starts as soon as possible after completion of treatment, and no later than 2 weeks after the last treatment session. The post-treatment testing corresponds to the baseline testing, with the exception of the DNA saliva sample, which is only provided at baseline.

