### Power analysis and statistical analysis

Power estimates were calculated using the G* Power 3 programme [103]. Treatment effects will be investigated by an intention-to-treat approach to data analysis using a hierarchical linear model, whereby therapists will be included at the second level to account for potential nesting by this factor. Power analysis for effects are estimated with conservative repeated measures analysis of variance (ANOVA) (within-between interactions). For the primary outcome measure, based on previous studies [22, 28], the difference in effect size is set to *d* = 0.35, alpha = 0.05, correlation between repeated measures 0.5, two measurements (pre/post), a total of 70 subjects (*n* = 35 in each group) yielding power above 0.82. Moderators and mediators will be investigated using linear multiple regression, fixed model, single coefficients. An effect size set to *f*^*2*^ = 0.15, two-tailed tests, alpha = 0.05 and *N* = 70 yields power above 0.95 with four predictors. For the subset of functional MRI (fMRI) assessments the following statistics and power analysis will be applied: task-fMRI data will be analysed using General Linear Model in SPM12 for pre-processing and single subject and group analyses, GIFT [104] to investigate the functional and structural data, and arterial spin labelling (ASL) data will be analysed in SPM12. Region of interest (ROI) will be analysed for both structural and functional data (SPM12) to extract blood oxygen level dependent (BOLD) responses to test correlation with specified variables. Expecting percent signal changes of approximately 0.5% at the single voxel and spatial smoothing at full width at half maximum (FWHM) of 5 mm (provides an estimated effect size of *d* = 0,7), using the two-tailed independent samples *t* test, an allocation rate of 1, alpha set to 0.05, correlation between repeated measures 0.5 and a total sample size of 80 (40 in each group) yields power above 0.87. For differences between pre-treatment and post treatment data using the same parameters, the matched-pairs *t* test with 20 subjects yields power above 0.90. Treatment effects are estimated using conservative repeated measures ANOVA (within-between interaction), and conservatively setting the estimated value of *d* = 0.35, alpha set to 0.05, two measurements (pre, post), correlation between repeated measures 0.5, and 60 subjects (*n* = 20 per group) yields power above 0.83. Based on these calculations, the estimated power values indicate that risk of committing type II errors is adequately controlled.

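### Ending trial participation, not only study treatment, when an exclusion condition arises after randomisation creates outcome-related missing PSWQ and undermines the intention-to-treat analysis

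*Protocol article*

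**What the plan says.** All of this is in the protocol article.

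- **Randomisation:** "Randomisation is performed anonymously at the University of Bergen in blocks of ten following baseline testing". Anything that happens during treatment therefore happens to a randomised participant.
- **Ethical considerations:** "If conditions that exclude patients from participating in the study are disclosed or develop during treatment, the participant will be discontinued from trial participation". The next sentence adds that "the participant will continue treatment or be referred for other suitable treatment, depending on the reason for discontinuing trial participation".
- **Participants:** criterion 3 is "changes in the dose of other psychotropic medication during the study". The list also covers benzodiazepine and antipsychotic use, severe major depression, other psychotherapy, medical conditions that rule out exercise, and (criterion 10) "participation in physical exercise exceeding 75% of the exercise dose given in the study".
- **Power analysis and statistical analysis:** "Treatment effects will be investigated by an intention-to-treat approach to data analysis using a hierarchical linear model". Missing data are to be handled inside that model, with last observation carried forward where the model does not apply.
- **Post-treatment testing:** it takes place "no later than 2 weeks after the last treatment session".
- **Pre-treatment period:** a participant who completes too few sessions still goes on to interim testing.

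**The concern.** Intention-to-treat needs outcomes from everyone randomised, whatever happens to their treatment. The rule under Ethical considerations separates trial participation from treatment and stops the one the analysis needs. Treatment may go on or be replaced, while nothing in the article says that assessment goes on.

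The losses would not be random. Criterion 3 is worded as an event during the study, and in an anxiety trial a dose change is a natural response to lack of improvement. Starting a benzodiazepine, becoming severely depressed or seeking other psychotherapy can have the same origin. A participant discontinued during the CBT phase would have at most baseline and interim PSWQ, with no value after CBT.

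A likelihood model that assumes missing at random can use those earlier scores. It cannot recover a worsening that occurred after them and that caused the discontinuation. If this happens more often in one arm, the PSWQ comparison is biased. In either case the analysed sample is smaller than the 70 on which power was based. Outcomes that were never collected cannot be restored by any later analysis plan.

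**Working it through.** **1. The plan's own power figure.** Inputs from Power analysis and statistical analysis: d = 0.35, alpha = 0.05, correlation 0.5, two measurements, N = 70 (35 per arm), repeated-measures ANOVA, within-between interaction.

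- f = d/2 = 0.175
- Noncentrality = f² × N × m / (1 − r) = 0.030625 × 70 × 2 / 0.5 = 8.575, with 1 and 68 degrees of freedom
- Power = 0.823, which reproduces the stated value above 0.82. This requires all 70 to have pre and post values.

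**2. Power if the rule costs post-treatment values.** Same formula at reduced N. The loss rates are assumptions, as the article gives none. The last column is 70 / (1 − loss), rounded up.

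| Loss | N left | Power | Randomised to keep 70 |
|---|---|---|---|
| 5% | 66 | 0.800 | 74 |
| 10% | 63 | 0.781 | 78 |
| 15% | 60 | 0.760 | 83 |
| 20% | 56 | 0.730 | 88 |

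**3. Bias in the arm difference.** A simulation with 400,000 per arm used baseline, interim and post scores with pairwise correlation 0.5, so that the SD of change is 1. Each participant had a discontinuation score s × (change, centred within arm) + √(1 − s²) × noise. The participants with the highest scores in each arm, up to the assumed rate, lost their post value. The values of s were 0 (no link to outcome), 0.5 (moderate) and 1 (the worst responders are exactly the ones lost). Post was then regressed on arm, baseline and interim among those observed, as a close stand-in for a missing-at-random likelihood model.

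Results for a true difference of zero, in SD of change; positive favours exercise:

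| Loss, exercise / telephone | s = 0 | s = 0.5 | s = 1 |
|---|---|---|---|
| 10% / 10% | −0.001 | +0.002 | −0.003 |
| 15% / 5% | +0.002 | +0.057 | +0.121 |
| 5% / 15% | +0.001 | −0.056 | −0.120 |
| 20% / 5% | 0.000 | +0.086 | +0.180 |
| 5% / 20% | +0.001 | −0.081 | −0.181 |

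With a true difference of 0.35, the 15% / 5% case is estimated at 0.405 to 0.474, and the 5% / 15% case at 0.292 down to 0.227.

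**4. Scale.** 15% and 5% of 35 are 5.25 and 1.75, so about five people against two. The planned effect in SD of change depends on how d is read. Taken directly as the arm difference in change it is 0.35. The noncentrality of 8.575 implies 2 × √8.575 / √70 = 0.70. A bias of 0.06 to 0.12 is therefore 17% to 34% of the planned effect on the first reading (0.06/0.35, 0.12/0.35) and 9% to 17% on the second (0.06/0.70, 0.12/0.70).

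**The case against.** The rule concerns participation, and the statistics section concerns analysis. Nothing says that a discontinued participant's data are deleted, and the hierarchical model can keep baseline and interim scores. A reader might infer that the rule defeats intention-to-treat outright. The article does not support that; it supports only that the rule undermines it. This part of the objection stands.

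A reader might also infer that criterion 10, carried into treatment, would discontinue every adherent CBT + PE participant. Its natural meaning is habitual exercise at entry, and the other reading would have the trial empty its own exercise arm. The point does not rest on it.

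Several other criteria also read as entry screens. Severe depression is determined by the M.I.N.I., which the Measures and Recruitment sections place before inclusion, and the visible text describes no repeat. A condition merely disclosed during treatment may predate randomisation and have nothing to do with outcome or arm. This also stands, and it narrows the firm ground to criterion 3, with the other conditions only plausible.

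The rule is worded identically for both arms, so unequal loss is an inference, and the rates used here are assumptions.

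Finally, a condensed article may leave the follow-up of discontinued participants to the full protocol. That would excuse silence. Here the article states a rule, and as written it ends trial participation. Its provision for participants with too few sessions shows that non-attendance alone does not stop testing, but nothing comparable is stated for those discontinued under this rule.

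**Conclusion.** The concern holds in this form: by ending trial participation for randomised people on grounds that can follow from poor response, the protocol creates outcome-related missing PSWQ after treatment and at follow-up. This sits badly with the intention-to-treat analysis it declares, and missing-at-random handling only partly helps.

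Size and direction are unknown. Under an assumed loss of 15% against 5%, the bias is about 0.06 to 0.12 SD of change. The upper end assumes that discontinuation tracks outcome perfectly. The sign reverses if the rates reverse, and the bias is near zero if loss is unrelated to outcome or if loss and its link to outcome are equal across arms. A reader might infer that the rule favours the exercise arm, but the documents give no basis for a direction.

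The loss of power needs no assumption about unequal arms. N = 70 gives 0.823 only with complete pre and post values; a 10% loss gives about 0.78 and a 15% loss about 0.76.

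**What to change.** Leave clinical decisions about treatment exactly as they are, and separate them from outcome collection:

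- Amend Ethical considerations so that every randomised participant, unless consent is withdrawn, is still invited to the PSWQ and ADIS-IV assessments at the dates they would have been due. Because post-treatment testing is timed from the last session, state how that date is set for someone who stops early.
- State that all randomised participants are analysed in the arm allocated.
- Record a dose change, new medication or new psychotherapy after randomisation as an intercurrent event, and report numbers and reasons by arm. Add a sensitivity analysis that allows the remaining missing values to depend on unobserved outcome.
- Reconcile the Participants, Ethical considerations and statistical sections by saying when each exclusion criterion applies, including that criterion 10, as its wording suggests, is a criterion for entry.

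The cost is a short amendment and a few extra assessments in people already enrolled. The downside is that some outcomes will reflect care outside the protocol, which an intention-to-treat comparison accepts.
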